### Quality control

This trial is conducted in accordance with standard operating procedures for clinical trial management. All investigators have been authorized by the principal investigator, and have undergone appropriate training. A Trial Steering Committee is established to provide overall supervision of this study, and includes the principal investigator, as well as independent clinical and methodological experts. All granules are stored, managed, dispensed, and retrieved by professional pharmacists.

## Discussion

Our team has studied the formula and its main components for several years. We have found that Yiqihuoxue decoction (three herbs contained in YQYYHX) improved the BG, lipids, interleukin-6 (IL-6), tumor necrosis factor-α and aortic plaques in ApoE^−/−^ mice, while it increased the methylation of *AKT1, Nr1h3*, and *Fabp4* (30). Xiongshao Capsule (two herbs contained in YQYYHX) reduced the myeloperoxidase, total and free cholesterol in aorta wall cells of rabbits (31). Then we analyzed previous clinical prescriptions of the principal investigator and identified several herbs commonly used to treat patients with T2DM and EVA. Based on TCM theory and the above research foundation, we developed YQYYHX formula and prepared it as granules to improve the stability of its components. In unpublished studies, we also found that YQYYHX alleviated aortic plaques, reduced triglyceride and tumor necrosis factor-α in ApoE^−/−^ mice. Equol, a gut microbial metabolite derived from daidzein (one of the constituents of YQYYHX), has been reported to be associated with baPWV (32).

Arterial stiffness represents the risk of macrovascular complications in T2DM (33). PWV is used to evaluate arterial stiffness and vascular aging (34), defined as the ratio of the distance to the time traveled by the pulse wave between two specific sites. Although carotid-femoral PWV is commonly used for cardiovascular diseases, baPWV is easier and more convenient to test (35). It is used to measure the arterial stiffness of lower extremity arteries, whose normal range is below 1,400 cm/s. Age adjustment should be applied when assessing EVA. BaPWV is positively correlated with the risk of newly diagnosed diabetes in hypertensive patients (36). It is also positively correlated with aortic diameters of diabetic patients (37), while predicting risks of cardiovascular diseases (38). Patients with T2DM are more susceptible to coronary artery stenosis when baPWV exceeds 1,650 cm/s (39) and more susceptible to peripheral neuropathy when it exceeds 1,600 cm/s (40). It is positively correlated with heart rate, systolic blood pressure, triglyceride levels, and related indicators (41). Pathological baPWV is also correlated with 6MW distances (42) and UACR (43).

The normal range of ABI is 0.9–1.3. ABI < 0.9 indicates lower-extremity arterial stenosis or occlusion, while ABI > 1.3 indicates vascular calcification. ABI will decrease along with senescence (44), resulting in higher risks of cardiovascular events (45) and LEAD (46). As one of the key indicators for assessing glycemic control, HbA1c reflects average glycemic levels over the preceding 3 months. When it >7%, each 1% increase means 38% higher risk of macrovascular events of T2DM (47). It can also predict arterial stiffness (48). Lipid accumulation products have been shown to be positively correlated with baPWV (49). The triglyceride-glucose index also demonstrates a positive linear association with arterial stiffness (50, 51). As a characteristic of aging, systemic chronic inflammation can impair the clearance of senescent cells, weaken intrinsic tissue repair, promote immune-senescence, and induce cell death (52). Inflammation contributes to vascular aging by damaging vascular structures, disrupting functional homeostasis, and accelerating atherosclerosis. It is a marker of T2DM, EVA and atherothrombosis (53). IL-6 is a key cytokine implicated in promoting vascular cell senescence and senescence-associated mitochondrial dysfunction (54).

The 6 MW test serves as a valuable instrument for evaluating cardiopulmonary function. Specifically, it enables the assessment of ambulatory capacity, exercise tolerance, and muscle coordination in the lower extremities, with an opportunity to assess gait patterns. The 6 MW distance is negatively correlated with HbA1c levels, body mass index, and ages (55). VascuQol-6 is a simple and reliable instrument to assess the life quality of patients with intermittent claudication (56, 57). In our study, we also pay attention to changes in lower limb symptoms and TCM symptoms. Accordingly, we developed a symptom questionnaire and a TCM syndrome questionnaire by referencing relevant standards and guidelines. Patients with T2DM and EVA are more susceptible to renal damage (58). UACR is a relatively sensitive indicator for detecting early kidney injury.

This study provides an alternative and complementary therapy for patients with T2DM and EVA, who may benefit from it. This trial is designed with rigorous methodology and is expected to yield reliable results, providing high-quality evidence-based support (59) for clinical practice.

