### Inclusion criteria

Aged 40–85 years, regardless of sex.Meets the diagnostic criteria for T2DM.Evidence of lower extremity atherosclerotic plaques or stenosis, confirmed by Doppler ultrasound, CT angiography, or conventional angiography.Fontaine stage I–IIA.Meets the diagnostic criteria for EVA.Differentiated as “Qi-Yin deficiency with blood stasis” syndrome in TCM.Willing to sign the informed consent form.

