#### Secondary outcomes

Ankle–Brachial Index (ABI);

Fasting BG and HbA1c;

Lipid profiles;

Inflammatory cytokines;

6-min walk test;

Vascular Quality of Life Questionnaire-6 (VascuQol-6), symptom questionnaire, and TCM syndrome questionnaire (Tables S1–S3).

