#### Outcome analysis

All data will be analyzed using SPSS 26.0 after unblinding. Continuous outcomes will be initially assessed for distributional characteristics by Shapiro-Wilk test. For approximately normally distributed outcomes, *t*-tests or ANCOVA will be applied to compare groups; for variables with marked deviation from normality, nonparametric alternatives such as the Mann–Whitney *U*-test and Wilcoxon signed-rank test will be considered. The categorical variables will be analyzed using the χ^2^ test.

Baseline covariates and other prognostic factors will be incorporated into ANCOVA models to improve estimation precision and control for residual confounding. Repeated measurements or longitudinal data will be analyzed using linear mixed-effects models, allowing for appropriate modeling of within-subject correlations, and evaluation of treatment-by-time interactions. The hierarchical testing procedure will be used to adjust multiple secondary outcomes. Sensitivity analysis will be conducted to reduce the impact of protocol deviations.

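### The general rule for continuous outcomes pools ABI values above 1.3, which the protocol reads as calcification, with values for which a fall is the adverse course; this dilutes and blurs a secondary comparison

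*Protocol article*

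**What the plan says.** All references are to the protocol article.

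- **Secondary outcomes** lists "Ankle–Brachial Index (ABI") first, with no direction of benefit, category or cut-off.
- **Discussion** gives a two-sided range, "The normal range of ABI is 0.9–1.3", and assigns a different disease to each side: "ABI < 0.9 indicates lower-extremity arterial stenosis or occlusion, while ABI > 1.3 indicates vascular calcification". The next sentence gives the only direction of harm in the document: "ABI will decrease along with senescence (44), resulting in higher risks of cardiovascular events (45) and LEAD (46".
- **Outcome analysis** sets a general rule. "Continuous outcomes will be initially assessed for distributional characteristics by Shapiro-Wilk test", and they then go to a t-test or ANCOVA, or to rank tests if markedly non-normal. "The categorical variables will be analyzed using the χ^2^ test". Nothing says that ABI is categorised or treated apart.
- **Inclusion criteria** require "Evidence of lower extremity atherosclerotic plaques or stenosis, confirmed by Doppler ultrasound, CT angiography, or conventional angiography", with T2DM, EVA and Fontaine stage I to IIA at ages 40 to 85. Neither the inclusion nor the exclusion criteria limit ABI.
- On multiplicity, Outcome analysis says "The hierarchical testing procedure will be used to adjust multiple secondary outcomes", without an order.

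**The concern.** A comparison of means or ranks is interpretable only if a higher value means the same thing for everyone compared. By the protocol's own account that holds for ABI up to about 1.3, where a fall signals stenosis, but not above it, where a high value signals calcification.

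A participant moving from 0.80 to 0.85 and one moving from 1.40 to 1.35 both approach the stated normal range, yet their changes of +0.05 and −0.05 sum to zero. A participant moving from 1.25 to 1.35 leaves the normal range on the calcification side, yet contributes +0.10, twice the gain of the first. Adjusting for baseline ABI with a linear term, or switching to ranks, keeps the assumption of a single direction.

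At stake is the reading of one secondary outcome: a real effect at the low end may be diluted, and part of a rise may not be improvement.

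**Working it through.** **The plan's own figure.** The only sample size given is for baPWV: 1600 ± 260 against 1440 ± 234 cm/s, two-sided α = 0.05, power 0.90, 52 per group. A Welch t-test gives power 0.8988 at 51 and 0.9044 at 52 per group, so 52 is reproduced. It says nothing about ABI, for which the document gives no effect, SD or power.

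**Inputs for ABI.** From the document: the limits 0.9 and 1.3, and the general analysis rule. Assumed, because the document gives none:
- pL and pH, the shares with baseline ABI below 0.9 and above 1.3;
- e = 0.05, the treatment shift towards normal in the low tail;
- r·e, the shift towards normal in the high tail;
- no shift inside the normal range;
- SD of the change from noise 0.06, with 52 per arm.

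**Mean difference.**
- Pooled, as the plan reads: e(pL − r·pH).
- Limited to baseline ABI ≤ 1.3: e·pL/(1 − pH).

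| pL | pH | Pooled, r = 0 | Pooled, r = 1 | Pooled, r = 2 | Baseline ≤ 1.3 |
|---|---|---|---|---|---|
| 0.4 | 0 | 0.020 | 0.020 | 0.020 | 0.020 |
| 0.4 | 0.1 | 0.020 | 0.015 | 0.010 | 0.05 × 0.4/0.9 = 0.022 |
| 0.4 | 0.2 | 0.020 | 0.010 | 0 | 0.05 × 0.4/0.8 = 0.025 |
| 0.2 | 0.05 | 0.010 | 0.0075 | 0.005 | 0.05 × 0.2/0.95 = 0.0105 |
| 0.3 | 0.3 | 0.015 | 0 | −0.015 | 0.05 × 0.3/0.7 = 0.021 |
| 0.2 | 0.4 | 0.010 | −0.010 | −0.030 | 0.05 × 0.2/0.6 = 0.017 |

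If the high tail does not respond (r = 0), the pooled figure is smaller only by the factor 1 − pH. If it responds, the loss is larger. The pooled difference is zero when r·pH = pL and changes sign only when r·pH exceeds pL.

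**Power, r = 1.** In the treated arm the variance of change is 0.06² + e²[(pL + pH) − (pL − pH)²]; in the control arm it is 0.06². For pL = 0.4 and pH = 0.1:
- Pooled: 0.0036 + 0.0025 × (0.5 − 0.09) = 0.004625. SE = √[(0.004625 + 0.0036)/52] = 0.01258. z = 0.015/0.01258 = 1.19, power about 22%. Simulation with 3000 runs also gave 22%.
- Baseline ≤ 1.3: the low share is 0.4/0.9 = 0.444 and n = 52 × 0.9 = 46.8 per arm. Variance = 0.0036 + 0.0025 × 0.444 × 0.556 = 0.004217. SE = √[(0.004217 + 0.0036)/46.8] = 0.01292. z = 0.0222/0.01292 = 1.72, power about 40%.

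The same steps with pH = 0.2 give about 12% pooled (z = 0.010/0.01286 = 0.78) and about 45% restricted (z = 0.025/0.01371 = 1.82, n = 41.6 per arm). With pH = 0 both are 37%. With r = 0 and pH = 0.1 the pooled power is 37% against 40% restricted, so the gain is then small.

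**The case against.** The strongest reply is that no sentence names an ABI analysis. The rule is general, and the statistical analysis plan, which is not shown, may categorise ABI or deal with values above 1.3. This stands as a limit on the point, but does not remove it: a stated rule covers every continuous outcome, and it fits badly with the meaning that the same document gives this variable.

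Four stronger readings are tempting, and the documents do not support them.

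- **That ABI has no clinical direction at all.** The Discussion names a falling ABI as the adverse course, so a direction exists; it fails only for high values.
- **That the entry criteria select for both tails.** They require plaque or stenosis, which points to low or normal ABI. EVA is defined by age-adjusted PWV alone, and nothing links it to ABI above 1.3. High values are merely not excluded.
- **That benefit will cancel or appear as harm.** This needs r·pH at or above pL, which is less likely in a cohort chosen for plaque or stenosis. No shares are given, and no section suggests that calcified vessels would respond within 12 weeks.
- **That a misleading ABI result would block or open the other secondary outcomes.** ABI is listed first, but the testing order is not stated.

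Scoring the distance from 0.9 to 1.3 would hold its sign under the assumptions above, but it is a debatable trade. It ignores a fall from 1.20 to 0.95, and it would score worsening stenosis in a participant starting at 1.40 as benefit. It is therefore not proposed here.

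**Conclusion.** The point holds as a minor one. Under the rule as written, any participants with ABI above 1.3 dilute the group comparison and blur what a difference means. The dilution ranges from slight, if they are few or do not respond, to substantial: with 40% low and 10% high ABI and equal response, the pooled difference is 0.015 rather than 0.022. These figures rest on assumed shares, effect and SD; the direction of the argument rests on the document alone. Only one secondary outcome is touched. The baPWV primary analysis, the 52 per group behind it and the total of 120 do not change.

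**What to change.** Before unblinding, and preferably before the planned interim analysis, specify that:

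1. the main ABI comparison takes higher as better, adjusts for baseline ABI, and is limited to participants with baseline ABI of 1.3 or less;
2. participants with baseline ABI above 1.3 are reported separately by arm;
3. the number in each arm who cross above 1.3 during treatment is reported beside the main result, so that such a rise is not read as improvement.

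Because the restriction uses a baseline value, the comparison stays randomised within the subgroup. Item 3 is needed because the restriction alone would still count a move from 1.25 to 1.35 as a gain.

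The cost is a few sentences and no new data. The ABI comparison loses the participants who start above 1.3: at an assumed 10%, about 5 of 52 per arm (52 × 0.1 = 5.2). If the statistical analysis plan already contains an equivalent rule, a cross-reference is enough.

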### Trial status

Until March 10, 2026, 72 participants have been enrolled, and 38 have completed the observation period.
